**Figure 4. F4:**
[figure not shown]
Neuromuscular electrical stimulation (NMES) applications: (A) passive; (B) with active wrist extension; and (C) with functional task.

### NMES Training Protocol

In this group, each session will include 20 minutes of NMES and 40 minutes of conventional exercises. The NMES intervention will be applied progressively over an 8-week period as follows:

Weeks 1‐2: Participants will receive passive NMES application.Weeks 3‐5: NMES will be combined with active wrist extension. During the rest phase, the wrist will be maintained in a neutral position, while in the stimulation phase, participants will be instructed to actively perform wrist extension movements.Weeks 6‐8: NMES will be integrated into functional tasks. During the rest phase, participants will practice grasping objects of varying sizes (eg, balls), while in the stimulation phase, they will be instructed to release the object through active wrist extension.

### Leap Motion–Based Exercise Group

The Leap Motion–based VR system consists of a personal computer and an LMC, which are connected via a USB. Using infrared technology, the Leap Motion device allows for the tracking of multiple hand and finger movements without the need for markers or data gloves [20]. The Fizyosoft Becure company has developed software integrated into the Leap Motion system, creating task-oriented games designed to improve grasping ability and hand activities in individuals with upper extremity limitations. These games represent the first Turkish-language software developed for the Leap Motion system [45]. Each session of the VR intervention will last for 20 minutes and will use games developed within the Becure HandROM platform.

#### Leap Ball

Involves grasping a ball by activating all interphalangeal flexors followed by interphalangeal and wrist extensors and then placing the ball into designated holes.

#### bRabbit

Requires repetitive wrist flexion and extension to jump over snakes and hide from flying birds.

#### Pong

Focuses on repetitive wrist flexion and extension to hit rapidly incoming balls, with increasing speed and frequency.

All games will be progressively adapted to ensure advancement, with modifications specific to each game. The Pong game is expected to be more challenging compared to the others; therefore, it will be introduced starting from the third week of intervention. Prior to the intervention, children will be introduced to the Leap Motion sensor and games, including instructions about optimal positioning relative to the sensor and game-play mechanics. They will also be provided an opportunity to practice before the actual intervention begins. During the sessions, compensatory movements will be prevented by the supervising physiotherapist. Each game will be adjusted to the child’s needs, starting from an appropriate difficulty level. Progression across weeks will be achieved by modifying parameters (such as game speed, trial repetitions, and the size or number of balls/holes) (Figure 5). During sessions, children will be monitored for fatigue, discomfort, dizziness, or any adverse response. Rest breaks will be provided when needed. Any adverse events will be recorded, and the session will be stopped if necessary.

**Figure 5. F5:**
[figure not shown]
Leap motion-based serious game screenshots and game-play.

### Leap Motion–Based Training Protocol

In this group, each session will consist of 20 minutes of Leap Motion–based training and 40 minutes of conventional exercises. The Leap Motion–based intervention will be conducted over an 8-week period with progressive difficulty as follows:

Weeks 1‐2: participants will begin with introductory sessions consisting of VR-based exercises using the Leap Ball and bRabbit games.Weeks 3‐5: training difficulty will be increased by adjusting game parameters such as speed, number of repetitions, number, and size of balls/targets, according to each child’s individual level. The game set will include Leap Ball, bRabbit, and Pong games.Weeks 6‐8: the same progression strategy will be maintained, with further increases in task complexity through modifications in game parameters (eg, speed, repetitions, number, and size of balls/targets). The game set will again include Leap Ball, bRabbit, and Pong games.

### Statistics

Statistical analyses will be performed using SPSS for Windows (version 25.0; IBM Corp). Descriptive statistics will be calculated for all variables. Continuous variables with normal distribution will be presented as mean (SD), continuous variables without normal distribution as median (minimum-maximum), and categorical variables as frequency and percentage. The normality of continuous variables will be assessed using the Shapiro-Wilk test. The primary intervention effects will be analyzed using a 2-way repeated measures ANOVA to evaluate the main effects of group and time, as well as the group×time interaction. When significant main or interaction effects are detected, post hoc pairwise comparisons will be performed with Bonferroni correction for multiple comparisons. For variables that do not meet the assumptions for parametric analysis, appropriate nonparametric alternatives will be used. Categorical variables will be analyzed using the chi-square test or Fisher exact test, depending on the expected cell counts. The primary analysis will be conducted as a complete-case analysis, including only participants who complete all assessment time points. Dropouts and missing data will be documented. Effect sizes will be reported to support the interpretation of the magnitude of intervention effects. Partial eta squared will be reported for repeated measures ANOVA results. A *P* value of <.05 will be considered statistically significant.

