### Outcome Measures

The primary outcome of this study is hand function, and the secondary outcomes are wrist extensor and flexor muscle activation, wrist ROM, wrist selective motor control, and hand use in daily activities. The baseline assessments (T0) will be done after enrollment. Before randomization, all participants will complete a 4-week standardized upper extremity–focused conventional therapy program, which will be conducted as a baseline standardization period to reduce the potential influence of previous routine rehabilitation programs. This phase will not be considered part of the randomized intervention comparison. Postconventional exercise assessments (T1) will be conducted after a 4-week conventional therapy program. Randomization will be performed after the T1 assessment to allow comparison of the additional effects of NMES and Leap Motion–based training when added to the standardized conventional exercise program. The final assessments (T2) will be performed after 8-week NMES and Leap Motion–based interventions. The main comparison will be based on the change from T1 to T2 between the intervention groups. A randomized controlled design was selected to minimize selection bias and to ensure balanced baseline characteristics between the intervention groups. The inclusion of 3 assessment time points (T0, T1, and T2) allows differentiation between the effects of conventional therapy and intervention-specific effects.

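### The primary analysis does not single out the declared main comparison, the between-arm difference in T1-to-T2 change, as the one primary test

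*Protocol article*

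**What the plan says.** **Outcome Measures** fixes the comparison: "The main comparison will be based on the change from T1 to T2 between the intervention groups". On timing it says "Randomization will be performed after the T1 assessment", so T0 and T1 both precede allocation. Of the four-week conventional programme between them it says "This phase will not be considered part of the randomized intervention comparison".

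**Statistics** sets the primary analysis: "The primary intervention effects will be analyzed using a 2-way repeated measures ANOVA to evaluate the main effects of group and time", and the same sentence goes on to include the group×time interaction. It then adds: "When significant main or interaction effects are detected, post hoc pairwise comparisons will be performed with Bonferroni correction for multiple comparisons". Significance is P<.05 throughout, and the effect size named for the ANOVA is partial eta squared. No term is designated as the test of the main comparison.

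The Statistics section does not list the visits that form the time factor. Two statements point to all three: "The primary analysis will be conducted as a complete-case analysis, including only participants who complete all assessment time points", and, in Outcome Measures, "The inclusion of 3 assessment time points (T0, T1, and T2) allows differentiation between the effects of conventional therapy and intervention-specific effects".

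**The concern.** The article defines a single 1-df question and then plans a family of tests without saying which one answers it. With three visits in the model, none of the listed tests is exactly that contrast:

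- **Group×time** has 2 df. It is sensitive to the T1-to-T2 difference, but also to arm differences in T0-to-T1 change, which can only be chance because allocation comes later.
- **Group** averages T0, T1 and T2, so two thirds of its weight lies on visits that treatment cannot have affected.
- **Time** does not compare NMES with Leap Motion, yet a significant time effect opens the post hoc tests.
- **Pairwise comparisons of means** are, on the usual reading, within-arm or single-visit contrasts. Neither is a difference in change.

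What is at stake is which p-value carries the conclusion. A positive claim could rest on a term that does not answer the declared question, and the choice of term could be made after the results are seen. Partial eta squared also has no direction and no seconds, whereas the hypothesis is directional and the Discussion interprets the Jebsen-Taylor test against 54.7 and 20.9 seconds.

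**Working it through.** **1. The plan's own figure.** Inputs from Participants: f = 0.5, power 95%, α = .05, minimum N = 24, attrition 20%, final N = 30. For a within-between interaction with m visits and correlation ρ, λ = f²·N·m/(1−ρ), with df (m−1) and (N−2)(m−1).
- m = 3, ρ = 0: λ = 0.25×24×3 = 18, df 2 and 44, power 0.965. N = 22 gives 0.948, so 24 is the minimum.
- m = 2, ρ = 0.2: λ = 0.25×24×2/0.8 = 15, df 1 and 22, power 0.959. N = 22 gives 0.941, so 24 again.
- Attrition: 24/(1−0.2) = 30.

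The figure is reproducible, but under settings that the article does not state. It therefore does not settle whether two or three visits enter the ANOVA.

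**2. If only T1 and T2 enter.** The interaction p-value equals that of the t-test on T1-to-T2 change (largest simulated difference below 1e-14). The interaction would then be the declared comparison.

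**3. If T0, T1 and T2 enter.** Assumptions, none given in the document: normal data, unit SD at each visit, equal correlation ρ between visits, 12 per arm (the minimum N of 24), and a true arm difference of 0.8 SD at T2 only.

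- *Group main effect.* Expected difference 0.8/3 = 0.267 SD. The standard error is √((1+2ρ)/3)·√(2/12), which is 0.333 at ρ = 0.5 and 0.380 at ρ = 0.8. The ratios are 0.80 and 0.70, and simulated power is 10 to 12%.
- *Interaction.* The arm differences (0, 0, 0.8) deviate from their mean by (−0.267, −0.267, 0.533), with sum of squares 0.427. So λ = (12/2)×0.427/(1−ρ) = 2.56/(1−ρ), or 5.1, 8.5 and 12.8 at ρ = 0.5, 0.7 and 0.8.
- *ANCOVA on T1 and T0.* Residual variance is 1 − 2ρ²/(1+ρ), or 0.667, 0.424 and 0.289.

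Simulated power:

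| Test | ρ = 0.5 | ρ = 0.7 | ρ = 0.8 |
|---|---|---|---|
| Group main effect | 12% | 11% | 10–11% |
| T1-to-T2 change score | 47% | 67–68% | 84–85% |
| Group×time, three visits | 49% | 71–72% | 88–89% |
| ANCOVA of T2 on T1 and T0 | 58–59% | 78% | 91% |

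**4. Error rates with no effect anywhere.** The interaction alone rejects in about 5% of trials. Group or interaction rejects in 9.3 to 9.8% across runs (two independent tests: 1 − 0.95² = 9.75%). About half of the falsely significant interactions occur without a significant T1-to-T2 difference.

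**5. Sensitivity to the pre-randomisation phase.** Suppose a 0.5 SD arm difference is built into T0-to-T1 change, with equal T1-to-T2 change. The three-visit interaction then rejects in 22 to 58% of trials (ρ 0.5 to 0.8, 12 to 15 per arm), against 5% for the T1-to-T2 contrast. This is conditional on such an imbalance.

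**6. Post hocs opened by time.** Suppose both arms improve equally, by 0.3 SD from T0 to T1 and 0.5 SD from T1 to T2. The time effect is significant in 94 to 100% of trials. Within-arm T1-to-T2 tests at .05/3 then disagree between the arms in 31 to 50% of trials, although the arms do not differ. The Discussion expects both arms to improve, so the setting is realistic.

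**The case against.** The strongest reply is that the planned model does include the between-arm comparison of change. The group×time term is named, it contains the T1-to-T2 contrast, and it equals that contrast if only T1 and T2 are used. The complete-case sentence defines who is analysed, not the levels of the time factor, and Outcome Measures already places the earlier phase outside the comparison. A condensed article may leave the exact contrast to a fuller plan.

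Much of this stands. A reader might infer that the plan never tests its main comparison; the text does not support that. That T0 enters the model is an inference, though the natural one, since nothing limits the ANOVA to T1 and T2. A reader might also infer that the interaction has an inflated error rate. It does not: averaged over randomisation it holds 5%, and the 22 to 58% above is conditional. Nor does the article say that a significant group main effect would establish superiority, so the 9.5% applies only if either term is accepted as an effect.

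The precision argument is limited too. The three-visit interaction has slightly more power than the simple change score, so the loss is only relative to ANCOVA on T1 and T0.

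What does not stand is that the matter is merely omitted detail. The article states both the comparison and the primary analysis, and the second does not identify the first. It also lets any significant main effect open further tests at the same threshold.

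**Conclusion.** The point holds in this form: the Statistics section does not designate the test of the declared main comparison and leaves several p-values competing with it. On the three-visit reading, the interaction is a valid but unfocused 2-df test, the group main effect is nearly uninformative (about 10 to 12% power for 0.8 SD at T2), and the time effect and within-arm post hocs do not compare the arms. Treating either group or interaction as an effect roughly doubles the false-positive rate, to about 9.5%.

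Against the interaction, ANCOVA on T1 and T0 gains about 10 power points at ρ = 0.5, 6 to 7 at 0.7 and 2 to 3 at 0.8. These sizes rest on assumed normality, equal correlations, 12 per arm and a 0.8 SD effect. The mismatch between the two sections does not depend on those assumptions. The 2-df and group-average criticisms do depend on T0 being in the model.

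**What to change.** Name one primary test for the Jebsen-Taylor outcome: ANCOVA of the T2 value on group, with the T1 and T0 values as covariates. The T1-to-T2 contrast from a mixed model with common pre-randomisation means is an equivalent choice. Report the adjusted between-arm difference in seconds with its 95% CI, so that it can be read against the thresholds in the Discussion. State that this is the only primary p-value, and keep the three-visit ANOVA and its post hocs as descriptive.

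The cost is a few lines of analysis text and two covariate degrees of freedom, with no new data. Results reports 11 children enrolled as of June 2026 and analysis only after all have completed, so the change can still be made before any outcome analysis.

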## Methods

### Participants

The sample size was calculated using the G*Power (version 3.1.9.7; Heinrich Heine University Düsseldorf, Düsseldorf) program, with the Jebsen-Taylor Hand Function Test (JTHFT) selected as the primary outcome measure and an assumed effect size of *f*=0.5 selected with reference to a previous study [26]. The calculation was performed with a statistical power of 95% and α=.05, in line with previous research using technology-assisted intervention in CP [27], yielding a minimum required sample size of 24 participants. Considering a 20% attrition rate, a total of 30 participants, with 15 participants in each group, was considered appropriate. The sample size calculation was based only on the primary outcome measure; secondary outcomes were considered exploratory and were not independently used for power estimation.

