### JTHFT

The JTHFT is a timed, 7-subtest assessment designed to evaluate hand functionality. The test is derived from common daily activities and includes the following tasks: writing a standardized 24-letter sentence, turning 5 cards, picking up small objects, picking up 5 beans using a spoon, stacking 4 checkers on a test board, moving 5 large empty cans, and moving 5 full cans. Since the study population includes children who may not yet be literate according to the age criteria, the first subtest (writing a sentence) will be omitted from the evaluation. Each subtest allows a maximum of 120 seconds for successful completion. All subtests are first performed with the nondominant hand, followed by the dominant hand. The validity and reliability of the JTHFT in children with CP aged 6‐18 years have been established by Tofani et al [34].

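### An assumption check on the trial data decides which test the primary outcome gets, and nothing ensures that the fallback keeps the declared T1-to-T2 comparison between groups

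*Protocol article*

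**What the plan says.** Under Participants, the sample size is calculated "with the Jebsen-Taylor Hand Function Test (JTHFT) selected as the primary outcome measure". Under JTHFT, the test is timed and "Each subtest allows a maximum of 120 seconds for successful completion".

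Under Outcome Measures, the question is fixed: "The main comparison will be based on the change from T1 to T2 between the intervention groups".

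Under Statistics, three sentences bear on the test:
- the model: "The primary intervention effects will be analyzed using a 2-way repeated measures ANOVA to evaluate the main effects of group and time", together with the group-by-time interaction;
- the check: "The normality of continuous variables will be assessed using the Shapiro-Wilk test";
- the switch: "For variables that do not meet the assumptions for parametric analysis, appropriate nonparametric alternatives will be used".

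The section does not say what is checked for normality (cells, pooled values, change scores or residuals), at what level, or which alternative follows. The switch applies to variables in general, and JTHFT is not excepted.

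**The concern.** The switch is a rule that the protocol states, so it is more than a missing detail. Whichever test is run on JTHFT, it is chosen after the data have been examined.

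The outcome makes the switch plausible. JTHFT consists of completion times with an upper limit, measured in children aged 6 to 15 with MACS levels 1-3. Skew and values at the limit are to be expected. With 12 to 15 children per arm, a normality test also rejects by chance if it is applied to several cells.

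What is at stake is the link between question and test. The ANOVA carries a group-by-time term. The fallback carries whatever the analyst considers appropriate at that time. A rank test of T1-to-T2 change between groups would keep the declared question. A rank test of T2 alone would ignore T1 and lose much of the power. The text allows both.

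**Working it through.** **The plan's own figure.** The inputs under Participants are "an assumed effect size of *f*=0.5 selected with reference to a previous study", 95% power and alpha .05. With 2 groups, m visits and correlation rho, the within-between interaction has lambda = f² × N × m / (1 − rho), on (m − 1) and (N − 2)(m − 1) degrees of freedom. For m = 3, rho = 0 and N = 24: lambda = 0.25 × 24 × 3 / 1 = 18 on 2 and 44 df, and power is 0.965. The stated 24 is reproduced, and 24 / (1 − 0.20) = 30. Neither m nor rho is stated, so these are settings that reproduce 24, not settings that the protocol gives. On them, the size refers to the ANOVA interaction and not to a rank test.

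**How often the switch occurs.** Assumptions, none of them in the protocol: 12 per arm (24 completers), correlation 0.8 between visits, Shapiro-Wilk at .05, times either normal or log-normal with log-SD 0.4 to 0.8.

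With independent tests of normal data:
- six group-by-visit cells: 1 − 0.95⁶ = 0.265;
- two change-score distributions: 1 − 0.95² = 0.0975.

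Simulation allows for the correlation:

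| What is tested | Normal data | Log-normal times |
|---|---|---|
| Any of six cells fails | about 25% | 67-98% |
| Either of two change-score distributions fails | about 8-10% | 23-65% |

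**Type I error.** With no effect, a switch applied rigidly with one fixed fallback gives 4.0-5.5% over 12 to 15 per arm and correlations of 0.5 and 0.8. If the smaller of the ANOVA-interaction and change-score rank-test p-values were reported, it would be 6.0-8.3%.

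**Power.** Effect of 0.8 SD at T2 (on the log scale for log-normal times), correlation 0.8, 12 per arm, six-cell switch:

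| Analysis | Normal | Log-normal, log-SD 0.6 |
|---|---|---|
| ANOVA interaction, no switch | 89% | 59% |
| Mann-Whitney on T1-T2 change | 81% | 63% |
| Mann-Whitney on T2 alone | 41% | 44% |
| Switch, fallback on change | 87% | 63% |
| Switch, fallback on T2 alone | 78% | 46% |

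The ANOVA and the rank test of change disagree on significance in 14% of these trials with normal data and 23% with log-normal times.

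**A fixed analysis for comparison.** Take an effect of 0.6 SD with the same correlation and size. Adjusting for T1 leaves a residual SD of √(1 − 0.8²) = 0.6, so the noncentrality is (0.6 / 0.6) × √(12 / 2) = 2.45. ANCOVA of T2 on group and T1 then has about 64% power with normal data, against 63% for the plan with its switch. With log-normal times, ANCOVA of log seconds has 63%, against 40-50% for the plan with its switch. The log analysis matches the model that generated these data, so that gain is a favourable case. It is smaller if the analysis stays in seconds.

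**The case against.** **The fallback.** A reader might infer that the fallback drops the group-by-time question and ends in separate within-arm tests. The protocol does not support this. It names no nonparametric test, and Outcome Measures fixes a comparison between groups that an appropriate alternative should serve. Mann-Whitney on T1-to-T2 change would serve it. Loss of the question is a risk, not a stated feature. It is also no fault of rank tests that they do not adjust for T1, because the planned ANOVA does not do so either.

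**The switch itself.** The text refers to assumptions for parametric analysis in general. That Shapiro-Wilk alone decides is the natural reading, not an explicit one. The six-cell rule is an assumption and the strictest reading. The log-normal model also ignores the 120-second limit. When six capped subtests are summed under assumed medians of 20-60 seconds, change scores fail in 9-42% of trials and the six-cell rule is met in 30-97%. The protocol does not say that the subtests are summed. So the switch may be common or fairly rare.

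**Error rate.** A reader might infer that the switch inflates type I error. With a fixed fallback it does not. Picking the smaller p-value would, but the protocol does not propose that, and Randomization and Allocation has the analyses done blinded to group. With skewed times, a switch to a rank test of change even does slightly better than the ANOVA kept throughout (63% against 59%).

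**Condensed article.** The name of a fallback may stand in a fuller plan that is not shown, so its absence here carries little weight. What remains is the rule itself: naming the fallback elsewhere would not stop the data from choosing the primary test.

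**Conclusion.** The point holds in a limited form. The Statistics section makes the primary test of JTHFT depend on an assumption check in the trial data, and it does not tie the alternative to the declared T1-to-T2 comparison between groups.

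The frequency runs from about 8-10% (normal data, change scores tested) to 67-98% (log-normal times, any of six cells). It rests on an assumed correlation of 0.8, 12 per arm and assumed distributions, because the protocol gives no SD, distribution or correlation for JTHFT.

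Type I error is not the problem. The harm is twofold: the primary test is not settled in advance, and two admissible choices would disagree in 14-23% of trials under the power settings shown; and power falls if the fallback uses T2 alone (from 87% to 78% with normal data, from 63% to 46% with skewed times). A T1-adjusted analysis fixed in advance loses nothing with normal data and can gain with skewed times. The change should be made, but it does not call the design into question.

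**What to change.** Remove the normality switch for JTHFT and fix one primary analysis now: a between-group comparison of T2 JTHFT adjusted for T1 (ANCOVA), with an estimate and 95% confidence interval. Choose the scale, seconds or log seconds, before the data are seen. If log seconds are chosen, also give the result in seconds, so that it can be read against the 54.7- and 20.9-second thresholds in the Discussion. The log scale and T0 as a further covariate are options, not requirements.

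Check model residuals only, and do not let that check change the primary test. Add one named robustness analysis that is run whatever the residuals show: a permutation p-value for the same model, or a rank test of T1-to-T2 change between groups.

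The cost is analysis wording only. The T1 and T2 measurements are already planned. The Results section reports 11 participants enrolled as of June 2026 and puts the analysis after all have finished, so there is still time.
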